### Reporting

This manuscript was prepared in accordance with the SPIRIT (Standard Protocol Items: Recommendations for Interventional Trials) checklist for clinical trial protocols. The completed checklist and Figure S1 can be found in Multimedia Appendices 1 and 2.

### Monitoring and Quality Assurance

Adherence to intervention protocols and the completeness and quality of study data will be monitored by the principal investigators or a designated study monitor. Electronic data capture on tablet devices and daily uploads to secure servers allow for the continuous monitoring of study activities in near real-time. All paper documents will be scanned. Rigorous quality assurance and quality control procedures will be established, including interviewer observation, validation and range checks during data entry, verification of entered data, and the monitoring of time stamps for electronic surveys.

### Patient and Public Involvement

Formative, qualitative work with HCT clients, CTC patients, and providers will elucidate key characteristics of CONSORT, including the selection of relevant social network contacts, appropriate message content for invitees, and defining parameters for the timing of invitation SMS text messages. Discussions will also focus on ethical considerations and the potential role of economic incentives as a means of motivating inviters to invite additional network contacts to test for HIV. Findings will be used to identify features of the CONSORT system that will maximize its acceptability among inviters and invitees.

### Ethical Considerations

This protocol was registered at ClinicalTrials.gov (NCT05967208) on July 25, 2023. The protocol was approved by the University of South Carolina Institutional Review Board (Pro00120208) in the United States; the Ethics Review Committee at Kilimanjaro Christian Medical University College (Protocol #1404); and the Tanzania National Institute for Medical Research (NIMR/HQ/R.8a/Vol.IX/4373). The project will consistently apply relevant ethical principles when working with individuals at risk for or affected by HIV. Protocol amendments will be submitted to these entities as required.

Informed consent documents will be developed in English and translated into Kiswahili. Trained research assistants will inform eligible individuals about the study’s purpose, procedures, risks, and benefits before obtaining informed consent for participation. The potential risks and benefits of research participation will be carefully explained in culturally appropriate and understandable language during the consent process. Consenting individuals will be enrolled in the study, with the study ID dictating their assignment to 1 of the 2 RCT study arms.

The data will be kept in compliance with relevant privacy regulations in Tanzania and the United States. Access to identifying information will be strictly limited. Study personnel will be instructed to keep the identities of all research participants confidential and will sign confidentiality agreements. The CONSORT system will be designed with a focus on confidentiality. Only encrypted versions of the invitee phone numbers will be stored in mParis, and information about the invitee will be stored separately from information about the inviter. Encrypted invitee phone numbers will be decrypted only as necessary for SMS scheduling and when "in flight" to the SMS text message center.

Inviters and their invitee testers who agree to participate in the research will receive between TSH 5000-10,000 (approximately US $2.20-US $4.40) as compensation for their time.

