**Methods:**

We will conduct the CONSORT study in Moshi, Tanzania, the commercial center and administrative capital of the Kilimanjaro Region in northern Tanzania. After qualitative formative work and pilot testing, we will enroll 400 clients presenting for HIV counseling and testing and 200 persons living with HIV and receiving care at HIV care and treatment centers as “inviters” into a randomized controlled trial. Eligible participants will be aged 18 years or older and live, work, or regularly receive care in Moshi. We will randomize inviters into 1 of 2 study arms. All inviters will be asked to complete a survey of their HIV testing and risk behaviors and to think of social network contacts who would benefit from HIV testing. They will then be asked to whom they would prefer to extend an HIV testing invitation in the form of a physical invitation card. Arm 1 participants will also be given the opportunity to extend CONSORT invitations in the form of automated confidential SMS text messages to any of their social network contacts or “invitees.” Arm 2 participants will be offered physical invitation cards alone. The primary outcome will be counselor-documented uptake of HIV testing by invitees within 30 days of inviter enrollment. Secondary outcomes will include the acceptability of CONSORT among inviters, the number of new HIV diagnoses, and the HIV risk of invitees who present for testing.

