#### Assignment to Study Arms

Participant IDs will be randomly assigned to either arm 1 or arm 2 using a random number generator. The random assignment is expected to result in approximately equal numbers of participants in each study arm.

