#### Blinding

Neither participants nor research staff will be blinded with respect to inviters’ study arm assignments.

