#### Social Network–Based HIV Testing Invitations

The enrollment survey will include a survey of inviters’ preferences for extending HIV testing invitations within their social networks. Participants will be asked to think of social network contacts across multiple network dimensions, including partners, family members, friends, coworkers, and other people who are aged 18 years or older and who would benefit from HIV testing. Participants will be asked to whom they would prefer to extend an HIV testing invitation through a physical invitation card; arm 1 participants will also be able to select CONSORT invitations. At the end of the survey, inviters will be given the respective number of coded invitation cards, and arm 1 inviters will be able to send CONSORT invitations to their network contacts (Figure 1).

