### Statistical Analysis

#### Analysis of the Primary Outcome

Efficacy will be analyzed descriptively by comparing, between the 2 study arms, the number of invitees testing for HIV within 1 month per 100 inviters (Figure 3). Analytically, efficacy will be modeled at the level of the inviter, using a zero-inflated negative binomial model, with the number of invitees returning for testing as the dependent variable. The primary explanatory variable will be a binary indicator variable for the study arm. Covariates will characterize variation in invitees’ testing uptake with inviters’ sociodemographic and network characteristics, HIV risk, and stigma.

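### The primary model can adjust for survey answers given after the arm is fixed, and nothing keeps the arm hidden until those answers are recorded

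*Protocol article*

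**What the plan says.** **Allocation.** Under Assignment to Study Arms, "Participant IDs will be randomly assigned to either arm 1 or arm 2 using a random number generator". Ethical Considerations places this at enrollment, after consent, "with the study ID dictating their assignment to 1 of the 2 RCT study arms". The abstract tells the steps in this order: "We will randomize inviters into 1 of 2 study arms. All inviters will be asked to complete a survey".

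**Blinding.** There is none for inviters' arm: "Neither participants nor research staff will be blinded" (Blinding).

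**Survey.** The Enrollment Survey section describes an interview, captured on tablets, that covers HIV-related behaviors, stigma, and demographic and socioeconomic items. The section on Social Network–Based HIV Testing Invitations makes the contact questions part of the same survey: "Participants will be asked to think of social network contacts across multiple network dimensions". Inviters are then asked whom they would invite by card, and arm 1 inviters may also choose CONSORT messages.

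**Analysis.** The section Analysis of the Primary Outcome plans a descriptive comparison of testers per 100 inviters by arm. It also plans a zero-inflated negative binomial model per inviter, with an arm indicator and covariates for inviters' "sociodemographic and network characteristics, HIV risk, and stigma".

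**The concern.** A covariate in a randomized comparison should be something that the arm cannot have changed. Here the arm exists before the survey answers do. The interviewer may know it, and the inviter may too. The prompt for contacts who would benefit from testing is elastic. Someone who knows that a confidential message is available may name more people, or different people, than someone who knows that only a card is on offer. The trial's own rationale makes this plausible: its second premise in the Discussion is that confidentiality encourages referrals within networks.

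If that happens, the number or type of contacts named lies on the path from arm to testers. Conditioning on it estimates the effect at a fixed contact list and leaves out the part that works through a longer list. The caption of Figure 2 claims an unbiased estimate of efficacy. That claim would still hold for the unadjusted comparison, but not for the adjusted model, which is the formal analysis.

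**Working it through.** The plan gives no figure on this point. Its only design figures are the detectable differences under Statistical Power, and this check does not depend on them.

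**Step 1: what is fixed, and when.**
- Arm: set by study ID at enrollment (Ethical Considerations; Assignment to Study Arms).
- Network, risk and stigma answers: collected in the enrollment survey.
- Order of randomization and survey: the abstract tells randomization first.
- Moment at which interviewer or inviter learns the arm: not stated.
- Safeguard that hides the arm until the answers are saved: none described.

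**Step 2: effect of adjusting for an arm-influenced contact count.** The inputs here are assumptions, because the protocol gives no estimate.
- R = true total rate ratio of testers per inviter, arm 1 to arm 2, set to 1.50.
- k = ratio of contacts named, arm 1 to arm 2, that is due to knowing the arm.
- Testers are proportional to contacts named.

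The total effect factors as R = k × (ratio of testers per contact named). A model that holds contacts named fixed returns the second factor, so adjusted ratio = R / k.

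- k = 1.0: 1.50 / 1.0 = 1.50
- k = 1.1: 1.50 / 1.1 = 1.36
- k = 1.2: 1.50 / 1.2 = 1.25
- k = 1.3: 1.50 / 1.3 = 1.15
- k = 1.5: 1.50 / 1.5 = 1.00 (the whole effect runs through contacts named)

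**Step 3: simulation check.** There were 600 inviters allocated by a fair coin, and 400 replicates. The control mean was 80 / 300 = 0.267 testers per inviter; 80 is one of the arm 2 counts listed under Statistical Power. Assumed besides: a mean of 4 contacts named in arm 2 and dispersion 1. A negative binomial model without a zero-inflation part was fitted with and without log contacts named.

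| Contacts named, arm 1 vs arm 2 | Unadjusted ratio | Adjusted ratio | Power, unadjusted | Power, adjusted |
|---|---|---|---|---|
| ×1.0 | 1.48 | 1.48 | 0.66 | 0.63 |
| ×1.1 | 1.51 | 1.38 | 0.69 | 0.47 |
| ×1.2 | 1.53 | 1.27 | 0.70 | 0.29 |
| ×1.3 | 1.51 | 1.16 | 0.69 | 0.14 |
| ×1.5 | 1.49 | 0.99 | 0.67 | 0.05 |

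The simulated ratios agree with R / k. The unadjusted ratio stays near 1.50 throughout. With no shift, adjustment does no harm.

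**Step 4: does the lack of stratified allocation add to the problem?** For the 200 CTC inviters, Binomial(200, 0.5) has a 95% range of 86 to 114 in one arm. Relative efficiency at that limit is 4 × 0.43 × 0.57 = 0.98. For the 400 HCT inviters the range is 180 to 220, and efficiency is 4 × 0.45 × 0.55 = 0.99. The loss is about 2% at most, with no bias.

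**The case against.** **The order is inferred.** Assignment and reveal are different events, and no section says that the arm is known when the contact questions are asked. The abstract, the description of the intervention and the section on invitations all put the contact question before the choice of invitation. This stands, and it means that arm influence is possible but not shown. It does not settle the matter, because asking about contacts first gives no protection if the arm is already known from the ID.

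**The mediator is not named.** The plan speaks of network characteristics without saying that the number of contacts named is one of them. Age, gender, past testing and past partners cannot be changed by the arm, although unblinded interviewing could still color self-reports of risk or stigma. The exact covariate list may properly sit in an analysis plan that is not shown. This also stands for the list. It does not extend to the order of data collection: once inviters have been surveyed with the arm known, no analysis plan can recover answers free of its influence.

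**The size is assumed.** No shift in contacts named can be read from the protocol, and zero is possible. The figures above are illustrations, and they assume strict proportionality.

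**Stronger readings.** A reader might infer that recruiters can foresee the next allocation because IDs are tied to arms. The protocol does not say that recruiters hold the list; it places assignment after consent and approaches clients consecutively. A reader might also infer that allocation should be stratified in blocks because the analysis is stratified by cohort. Simple randomization is unbiased, the gain would be about 2% at most, and blocks add some predictability in an open trial. Neither reading is supported.

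**Conclusion.** The point holds as a design risk, not as a demonstrated bias. As written, the formal primary model may condition on answers given after allocation, in an unblinded interview that contains an option for one arm only. If the arm changes the contacts named, the adjusted effect is pulled toward no difference: from an assumed 1.50 to about 1.36, 1.25 or 1.15 for 10%, 20% or 30% more contacts named in arm 1. With no such change there is no loss. The result rests on three assumptions: that the arm is known before the network answers are saved, that a contact count or type is among the covariates, and that uptake is proportional to contacts named. The descriptive comparison per 100 inviters is unaffected by this mechanism. The change is worth making because it is cheap and has to be made before enrollment.

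**What to change.** Program the tablet so that the risk, stigma and network-roster sections are completed and saved before the device shows the arm and opens the invitation menu. The link from study ID to arm can remain, provided that neither interviewer nor inviter sees it until that moment. The time-stamp checks already planned under Monitoring and Quality Assurance can confirm the order.

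In Analysis of the Primary Outcome, state that covariates are limited to answers recorded before the reveal or, failing that, to items that the arm cannot change, such as age, gender and testing history. Contacts chosen or added after the reveal should not be adjusted for.

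The cost is a reordered tablet form and possibly fewer covariates in the model. No extra visits or staff are needed, and the randomization method need not change.

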## Results

After qualitative formative work and pilot testing, enrollment in the RCT is expected to start in September 2024.

Research results from the CONSORT study will be disseminated through peer-reviewed publications, at national and international conferences, and through media outlets. To comply with the publication policies of the National Institute for Medical Research (NIMR) in Tanzania, approval for publications will be obtained from NIMR.

As many stakeholders and policy makers interested in this research reside in Tanzania, efforts will be made to translate the research abstracts into Kiswahili to make them more widely accessible. All system components and expertise needed to sustain and scale up CONSORT will be in place locally at the end of this project.

## Discussion

### Overview

This study will evaluate the acceptability and efficacy of automated, confidential SMS text message–based HIV testing invitations as a means of nudging individuals to test for HIV. If testing rates are higher in arm 1 invitees than arm 2 invitees, the results will support our hypothesis that an automated, confidential referral system is acceptable to both index participants (inviters) and referrals (invitees) and is effective for increasing uptake of HIV testing. If CONSORT is shown to be acceptable and effective, then confidential, digital, chain-referral methods could be used to improve the reach and cost-effectiveness of HIV testing efforts.

CONSORT’s potential is based on 3 key premises.

The first premise is that testing network contacts of persons living with HIV and those testing for HIV is an effective means for HIV case-finding. Identifying, tracing, and testing sexual contacts of persons with a sexually transmitted infection has been an essential component of public health sexually transmitted infection management for decades. Assisted HIV partner notification, by which health care workers elicit information about an index case's sexual partners and contact partners to request HIV testing, has been shown to be effective for increasing testing uptake and identifying new HIV infections [26-36]. A meta-analysis of 3 individual randomized trials [33-35] found that assisted partner notification, compared with passive referral, resulted in a 1.5-fold increase in HIV testing uptake. Moreover, the proportion of HIV-positive partners identified was 1.5 times higher with this approach [37]. Previous research also suggests that persons presenting for HIV testing have higher rates of HIV infection and higher rates of HIV risk behaviors than the general population [38,39]. Owing to similarities between members of social networks, a property known as homophily, referrals of HCT and CTC clients are, thus, also more likely to be infected with HIV than the general population. CONSORT*,* therefore, is well positioned to reach populations with an above-average risk of HIV infection and nudge them to test for HIV.

The second premise is that an assurance of confidentiality promotes referrals for HIV testing within social networks. CONSORT is conceptually related to confidential partner notification strategies [40,41], which are known to be highly acceptable to participants [42,43]. The evidence for technology-based notification systems for testing for sexually transmitted diseases, mainly derived from internet-based applications in high-income settings, is mixed: some show success [44-51], while others do not [41,52,53]. The efficacy of an impersonal, confidential approach to accessing network contacts in LMICs has yet to be evaluated. On the one hand, this approach may reduce the cost of contacting partners [54] and circumvent barriers such as nonreciprocal relationships [55], stigma [56], disclosure, and legal risks [57]. On the other hand, a confidential SMS text message is likely to be less motivating than personal communication. This study will compare the acceptability and efficacy of CONSORT versus other means of inviting social network contacts to test for HIV.

The third premise is that SMS text message–based nudges are inexpensive, effective tools for influencing health behaviors. Apart from incentives, reminders are among the simplest available nudging tools [58]. SMS text message–based nudges in the context of HIV testing remain rare, despite their low cost and nearly universal reach. While there is evidence that SMS text message–based interventions are feasible and acceptable in LMICs [59-63], and that nudging can influence health-related behaviors [64-66], relatively few studies have evaluated the use of SMS text messaging to encourage HIV testing [9,67-75]. We identified only 5 protocols that evaluated SMS text messaging for increasing uptake of facility-based HIV testing among at-risk adults in sub-Saharan Africa [9,70-72,75]. Although these studies demonstrated the strong potential of SMS text message–based messages to influence testing uptake, each has significant limitations, including using self-reports of HIV testing [67,70-72,75], using a combined intervention that included SMS text messaging with phone calls and in-person reminders [9], and limiting the intervention to young adults [9,72,74], women [72], or specific high-risk populations [71,75-82]. The design of this study is more rigorous in that (1) we will isolate the effect of SMS text messaging alone, and (2) actual testing uptake will be assessed in real time (rather than by self-report). Finally, results from CONSORT will be more broadly applicable, as the index (inviter) population will include participants from both sexes and across a greater range of ages, and it will extend beyond specific high-risk populations. With low costs of SMS text messages in the study area and an open-source and largely autonomous implementation, CONSORT may overcome the limits to growth encountered in traditional chain referral approaches [56] and support continuous, sustainable growth.

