### Study Aims and Hypothesis

This study aims to evaluate the acceptability and efficacy of automated confidential SMS text messaging–based HIV testing invitations as a means of “nudging” individuals to test for HIV. The overall study hypothesis is that an automated confidential referral system, developed and deployed in the Kilimanjaro Region of Tanzania, will be acceptable to both index participants (inviters) and their referrals (invitees), and it will be effective for increasing uptake of HIV testing. 

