### Secondary Outcomes

Secondary outcomes include the acceptability of CONSORT among inviters, the number of new HIV diagnoses, and the HIV risk among invitee testers. The assessments of secondary outcomes are detailed later on in their own section.

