#### Assessment of Secondary Outcomes

The acceptability of CONSORT among inviters will be described by the percentage of inviters extending at least 1 CONSORT invitation and the average number of CONSORT invitees per inviter. This outcome is assessed only for arm 1 participants.

For invitee testers, basic sociodemographic and risk characteristics (age, gender, marital status, pregnancy status, and previous testing), as well as their HIV test result, will be abstracted in aggregate form from administrative data collected for reports to Tanzania’s National AIDS Control Programme (NACP). Clients testing positive for HIV will be linked to care at a local CTC, following NACP guidelines [16]. Invitee testers consenting to become inviters will complete the same enrollment survey as their inviters, which includes a comprehensive HIV risk assessment.

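### Higher testing in arm 1 is to count as support for acceptability to invitees, but acceptability is defined and analysed for inviters only

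*Protocol article*

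**What the plan says.** Study Aims and Hypothesis states that the system "will be acceptable to both index participants (inviters) and their referrals (invitees), and it will be effective for increasing uptake of HIV testing". That is three claims: acceptable to inviters, acceptable to invitees, and effective.

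The Discussion (Overview) links the whole hypothesis to one comparison: "If testing rates are higher in arm 1 invitees than arm 2 invitees, the results will support our hypothesis", and the hypothesis is then restated with both groups named: "the results will support our hypothesis that an automated, confidential referral system is acceptable to both index participants (inviters) and referrals (invitees").

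The outcome sections are narrower. Under Secondary Outcomes: "Secondary outcomes include the acceptability of CONSORT among inviters, the number of new HIV diagnoses, and the HIV risk among invitee testers". Under Assessment of Secondary Outcomes: "The acceptability of CONSORT among inviters will be described by the percentage of inviters extending at least 1 CONSORT invitation", together with the mean number of CONSORT invitees per inviter, and "This outcome is assessed only for arm 1 participants". The only acceptability analysis is headed as being among inviters. The Abstract also lists acceptability for inviters alone.

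For invitees who test, the article describes a referral code or card, then "basic sociodemographic and risk characteristics (age, gender, marital status, pregnancy status, and previous testing), as well as their HIV test result", abstracted in aggregate. Invitee testers who consent to become inviters complete the same enrollment survey as their inviters.

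**The concern.** A hypothesis about how recipients regard an unsolicited SMS is to be supported by a count of people who tested. That count is the primary efficacy outcome. It was not defined as an acceptability outcome, and it says nothing about recipients who stayed away. If the Overview sentence is followed, a positive efficacy result would also be read as acceptability among invitees.

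That group deserves care. Limitations and Considerations acknowledges that their phone numbers are supplied without their consent, and it lists stigma and lack of trust in confidentiality assurances as remaining challenges. The article also makes its case for wider use conditional on CONSORT being acceptable as well as effective.

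**Working it through.** The article gives no figure for invitee acceptability, so there is nothing to reproduce. The check sets each part of the hypothesis against the outcomes, then asks whether the primary outcome could stand in for the missing one.

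**Step 1. Hypothesis against outcomes**

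- Acceptable to inviters: measured. Arm 1, share sending at least one SMS invitation and mean number of SMS invitees (Assessment of Secondary Outcomes); logistic and zero-inflated negative binomial models (Acceptability Among Inviters).
- Effective: measured. Testers within 30 days, compared between arms (Primary Outcome; Analysis of the Primary Outcome).
- Acceptable to invitees: no outcome, assessment or analysis is defined.

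**Step 2. Every contact with invitees or their proxies**

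- Testing site: code or card, aggregate characteristics, HIV result.
- Enrollment survey, only for testers who consent to become inviters: HIV-related behaviours, stigma, demographics and network preferences. No item on the SMS they received is described.
- 30-day phone survey: put to inviters who chose cards, about card distribution. Invitees are not contacted.
- Formative work (Study Timeline; Patient and Public Involvement): HCT clients, CTC patients and providers, before the RCT. Its stated use is to shape the system so that it is acceptable to both groups. That is design input, not a measurement in people who received a trial invitation.
- Invitees who do not test: no data.

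**Step 3. Could the primary outcome stand in?**

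It is expressed per 100 inviters, and in arm 1 it combines SMS and card testers. Testers per inviter = (invitations per inviter) × (testers per invitation), so it can rise through the first factor alone.

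Take the first scenario in Statistical Power: 20 testers in arm 2 and a difference of 7, hence 20 + 7 = 27 in arm 1. With 600/2 = 300 inviters per arm:

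- arm 2: 20/300 = 6.7 per 100 inviters
- arm 1: 27/300 = 9.0 per 100 inviters

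The ratio is 27/20 = 1.35. If arm 1 issues more than 1.35 times as many invitations as arm 2, testing per invitation is lower in arm 1 although testers per 100 inviters are higher. For example (assumed counts), with 300 invitations in arm 2 and 600 in arm 1, the figures are 20/300 = 6.7% and 27/600 = 4.5%.

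**Step 4. How many recipients the count leaves unobserved**

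The number of SMS invitations is not given. Assume 1 to 3 per arm 1 inviter, so 300 to 900 messages, each to a different recipient, and suppose that all 27 arm 1 testers came through SMS:

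- 27/300 = 9.0% tested, 91% unobserved
- 27/900 = 3.0% tested, 97% unobserved

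These percentages only illustrate missing information. Not testing is not evidence that the message was unwelcome.

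**The case against.** The strongest reply is that the article treats acceptability as behaviour throughout. For inviters it is sending an invitation, not an attitude score, so acting on the SMS is the parallel behaviour for recipients. This stands in part: testing after an SMS carries some information. But the article does not define it as an acceptability outcome, and the between-arm comparison pools SMS with cards and has no per-recipient denominator.

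A second reply is that the disputed sentence sits in the Discussion, while the outcome and analysis sections confine acceptability to inviters. That is right, and it makes the correction easy. It does not remove the conflict, because the hypothesis itself names invitees.

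A third is that an article leaves survey items to the full protocol. An item on the received SMS may exist there. It would still reach only testers who become inviters, and the Overview inference rests on testing rates, not on any such item.

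Some stronger readings are tempting and are not supported:

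- A reader might infer that invitees are seen only for a code and a test result. Some also complete the enrollment survey, and those offered the inviter role could themselves send invitations.
- A reader might infer that acceptability to invitees is ignored altogether. The formative work addresses it as a design aim.
- A reader might infer that most recipients object to the SMS. Nothing in the document shows this either way.

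**Conclusion.** The concern holds for the invitee part of the hypothesis. Two of the three parts have defined outcomes; acceptability to invitees has none, and the article proposes to support it from a comparison that is at most a weak, indirect indicator.

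This is more than condensed detail. The Overview states an inference that the listed outcomes cannot carry, and an analysis plan could not repair it without adding an outcome or changing the sentence.

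The reach is limited. Randomisation, the primary outcome and its model, and the listed secondary outcomes are untouched. It would go too far to say that the trial will inevitably report invitee acceptability, since the analysis sections plan no such result. The conclusion rests on the text alone. The 91% to 97% range depends on the assumed number of messages and is not needed for it.

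**What to change.** In Study Aims and Hypothesis and in the Discussion (Overview):

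1. Limit the acceptability conclusion to inviters.
2. Judge it on the two measures already defined for arm 1 inviters, not on testing rates.
3. Let the between-arm testing comparison support efficacy only.

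This is a change of wording, with no new data. The price is a narrower headline conclusion.

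If the invitee claim is to stay, define a separate measure at a contact that already exists and judge it apart from the primary comparison. For example:

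- an item on the received SMS in the enrollment survey of invitee testers who become inviters;
- a count of complaints to the phone number provided for invitees' questions, per 100 SMS sent.

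State that survey items cover only invitees who tested and agreed to become inviters. The cost is one survey item and a call log. Putting attitude items to all testing clients through counselors would cost more: it would need new individual data capture across the HCT facilities (25 in Moshi), where invitee characteristics are abstracted in aggregate, and it would still miss those who did not test. An opt-out count is not available as things stand, because the messages are described as one-way and no opt-out is mentioned.
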